### Participant timeline {13}

Participant recruitment will take place from January 2026 to July 2027. After recruitment and baseline assessment, dyads will be randomized. Dyads of the control group will receive the intervention for a duration of 12 months. The frequency of the intervention (meaning interactions with the Family Care Specialist) will be determined individually based on the stratification into low-, medium-, or high-strain group. Twelve months after baseline, the dyads will receive a follow-up assessment. The last intervention will thus be carried out in July 2028.

### Sample size {14}

Sample size was exclusively calculated based on a dichotomized threshold (≥ 12 months) of the PTS. Based on data from previous studies, 60% of informal caregivers of community-dwelling PlwD initially expressed their confidence in maintaining the informal care provision and the current care arrangements for at least 12 months. However, 10.5% of patients died and only 23% of the initial sample maintained this view one year later [21]. We, therefore, hypothesize that the intervention will increase this proportion to 35%, corresponding to an effect size of 0.25. Assuming a 1:1 randomization, statistical power of 80%, and a significance level of *α* = 0.05, a sample size of 224 dyads per group is required to detect a statistically significant effect based on a chi^2^ test. Considering an additional drop-out rate of 17.5%, summing up to 28% including death (in line with previously conducted study [43]), the target sample size increases to 272 dyads per group, resulting in a total of 544 dyads (1088 participants: 544 PlwD and 544 caregivers).

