**Methods:**

*Living@home* is a two-arm, randomized, controlled, multi-center interventional study designed to evaluate the effectiveness of a dyadic, app-based intervention on home care stability as well as the cost-effectiveness of this approach. The inclusion criteria are a formal diagnosis of dementia and living in their own home for the person with dementia, as well as access to a smartphone and internet for the informal caregiver. A total of 554 dyads will be recruited in five participating memory clinics and randomized (1:1 ratio, using block randomization) into either the intervention or the control group. The intervention group will receive personalized dementia care management for a period of 12 months. A mobile health app connecting caregivers with a Family Care Specialist offers informal caregivers access to memory clinics and Care Specialists at any time, monitoring of their health situation through real-time data collection, overview of care-related tasks, information and alerts tailored to the reported individual caregiver burden. The control group receives care-as-usual. Both groups will be assessed at baseline and after 12 months. The primary outcome is the caregiver’s perseverance time (Perseverance Time Scale), and crucial secondary supportive outcomes are neuropsychiatric symptoms in the person living with dementia (Neuropsychiatric Inventory), and the caregiver’s perceived burden (Zarit Burden Interview). Further secondary outcomes include the caregiver’s resilience and self-efficacy, the dyads’ physiological stress level (as measured by hair cortisol concentrations), health-related quality of life, caregiver depression and anxiety, dyads’ unmet needs, and cost-effectiveness. Intervention effects will be estimated by using multivariate regression analyses.

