### Recruitment {15}

Recruitment will be conducted in five participating memory clinics over 18 months. To reach the goal of 544 dyads in total (108 per study center), each clinic must recruit six dyads per month. To mitigate the risk of under-recruitment, several strategies may be employed, including allowing over-recruitment at individual sites to compensate for under-recruitment at others, engaging additional memory clinics proximate to the current study centers into recruitment activities, sending study invitations to potentially eligible participants via collaborating health insurance providers, maintaining a “waiting list” of interested dyads who contact the clinic up to 6 months before the recruiting phase, and informing and involving general practitioners in each region to support referrals. Participants who provide written informed consent to participate will subsequently be included in the study.

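### The enrolment target is given as both 554 and 544, the effect size of 0.25 does not match 23% versus 35%, and the dropout inflation presumes a handling of deaths that the described primary analysis does not provide

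*Protocol article*

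**What the plan says.** All references are to the protocol article.

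- **Abstract, Methods:** "A total of 554 dyads will be recruited in five participating memory clinics".
- **Sample size {14}:** "Sample size was exclusively calculated based on a dichotomized threshold (≥ 12 months) of the PTS". The control assumption is that "10.5% of patients died and only 23% of the initial sample maintained this view one year later". The intervention is expected to raise the proportion to 35%, "corresponding to an effect size of 0.25". With 1:1 allocation, 80% power, alpha 0.05 and a chi-square test, this gives 224 dyads per group. The next step reads "Considering an additional drop-out rate of 17.5%, summing up to 28% including death" and leads to 272 per group and 544 dyads in total.
- **Recruitment {15}:** "To reach the goal of 544 dyads in total (108 per study center), each clinic must recruit six dyads per month".
- **Criteria for discontinuing or modifying allocated interventions {11b}:** the caregiver's participation ends if the person with dementia dies.
- **Outcomes {12}, Primary outcome:** the PTS has six response options, from less than 1 week to 2 years or more. None stands for death.
- **Statistical methods {20a}:** the primary analysis is a proportional odds model on all six categories, by intention to treat.
- **Missing data {20c}:** multiple imputation may be used if data are missing at random. Death is not mentioned.

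**The concern.** There are three separate problems in the planning figures.

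1. The two targets, 554 and 544, cannot both be right, and the abstract is the part most often read and copied.
2. The effect size is presented as equivalent to 23% versus 35%, but it is not. A reader who starts from 0.25 will not arrive at 224.
3. The planning rates and the primary analysis appear to treat deaths differently. The 23% is a share of everyone who started, so people who died count as not maintained. The inflation follows that logic and allows only for the non-death loss. The primary outcome as described gives a dyad ended by death no value. The expected number with an observed outcome, and the population to which the 80% refers, therefore depend on a rule that the article does not state.

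**Working it through.** **Inputs (Sample size {14}).** p1 = 0.23, p2 = 0.35, power 80%, alpha 0.05 (taken as two-sided, which reproduces the plan's figure), deaths 10.5%, other loss 17.5%, total 28%.

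**1. Reproducing 224.** Pooled two-proportion formula without continuity correction:

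n = [1.960 × √(2 × 0.29 × 0.71) + 0.8416 × √(0.23 × 0.77 + 0.35 × 0.65)]² / 0.12² = 223.3, rounded up to 224. This matches, and power at 224 is 80.1%.

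**2. Reproducing 272 and the total.** 224 / (1 − 0.175) = 271.5, rounded up to 272; 2 × 272 = 544. Both match. Inflating for 28% would give 224 / 0.72 = 311.1, or 312 per group, so 272 covers the 17.5% alone. The figure of 554 would be 277 per group, which follows from no stated input.

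**3. Effect size for 23% versus 35%.**

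| Measure | Value |
|---|---|
| Cohen's h, 2·arcsin√0.35 − 2·arcsin√0.23 | 0.266 |
| Standardised difference, 0.12 / √(0.29 × 0.71) | 0.264 |
| Phi (w) | 0.132 |
| Odds ratio (log odds ratio) | 1.80 (0.589) |

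None rounds to 0.25. Had 0.25 been used as a standardised effect, the requirement would be 2 × (1.960 + 0.8416)² / 0.25² = 251.2, or 252 per group. The plan's 224 therefore came from the two proportions, not from 0.25.

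**4. Deaths and the number with an observed outcome.**

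- Deaths kept as failures: 544 × 0.825 = 448.8, about 224 per arm.
- Deaths without an outcome: 544 × 0.72 = 391.7, about 196 per arm.
- The difference is 544 × 0.105, about 57 dyads.

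**5. Power of the chi-square test under each reading.**

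| Reading | n per arm | Rates | Power |
|---|---|---|---|
| Deaths count as not maintained | 224 | 23% vs 35% | 80.1% |
| Survivors only, rates re-based | 196 | 25.7% vs 39.1% | 81.2% |
| Survivors only, rates not re-based | 196 | 23% vs 35% | 74.6% |

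The re-based rates are 0.23 / 0.895 and 0.35 / 0.895, assuming 10.5% mortality in both arms; 191 per arm would then suffice for 80%. The third row removes the deaths from n but keeps rates whose denominator includes them. It is consistent only if 23% and 35% were meant as rates among survivors.

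**6. The ordinal test.** The article gives no control distribution over the six categories, so any power figure rests on assumption. With 23% at 12 months or more, a common odds ratio of 1.80 and 196 per arm, Whitehead's formula gives about 86% to 91% for five assumed distributions. It gives about 81% for an extreme one with 70% in a single category.

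**7. Centre quota.** 544 / 5 = 108.8 per centre; 5 × 6 × 18 = 540.

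**The case against.** A reader might infer that the trial is under-inflated and has only about 75% power, because 28% loss is stated and 17.5% is used. The text does not support this. The 17.5% is described as additional to death, and the 23% is a share of the initial sample given directly after the 10.5% deaths. On that reading, inflating by 17.5% alone is right. The 75% mixes two denominators; with consistent denominators power is 80% or 81%. This part of the objection stands in full.

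A reader might also infer that the 80% is void because the chi-square test is not the primary test. The article discloses this openly: "Sample size was exclusively calculated based on a dichotomized threshold". If odds are proportional, none of the assumed distributions shows a shortfall for the ordinal model. The 108 per centre is rounding, and Recruitment {15} lets one site make up for another. Neither is a fault.

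It can further be said that an ordinal model can take death as its worst level, and that scoring of deaths is often left to the analysis plan, which is not shown. That is fair, and it rules out saying that the analysis excludes deaths. It does not remove the mismatch within the article: the planning rates count deaths, while the outcome scale and the discontinuation rule leave no place for them.

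Finally, nobody who reads the sample-size section will doubt that 544 is the derived target. That is true, but the abstract is still wrong.

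**Conclusion.** Two planning figures are wrong as printed. The abstract overstates the target by 10 dyads, since only 544 follows from the calculation. The effect size of 0.25 should be about 0.27. Neither changes the 224 per group.

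The third element is a mismatch to be reconciled, not a proven loss of power. The 17.5% inflation and the 80% hold if deaths count as not maintained. As described, the primary outcome would be observed in about 392 dyads (196 per arm). With rates re-based on survivors, power is then about 81%, assuming equal mortality in the arms. About 75% would apply only if 23% and 35% were survivor rates, which the wording does not suggest.

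These results take the article's description of the 23% at face value. They refer to the chi-square test used for sizing. The point should be fixed, towards the minor end; the sample size itself is not in doubt.

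**What to change.** 1. Change 554 to 544 in the abstract.
2. Replace the effect size of 0.25 with Cohen's h = 0.27, naming the measure, or delete it. The 224 stays.
3. Say how the death of the person with dementia enters the primary PTS analysis, and align the planning text with it. Either:
   - state that deaths enter as the worst outcome, in which case the 17.5% inflation and the 80% on the dichotomised scale stand; or
   - restate the planning on survivors: about 196 per arm, 25.7% versus 39.1% under equal mortality, power about 81%.

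The first two changes are wording only. The third also needs no further enrolment, but it is more than wording, because it fixes what the primary comparison estimates in a trial already recruiting. Recruitment began in January 2026, so 12-month outcomes are due from January 2027. The choice should be made and registered before outcome data are seen. If deaths become the worst level and the intervention does not affect mortality, the odds ratio at that cut would be 1, so the proportional odds assumption would need a comment.

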### Recruitment {15}

Recruitment will be conducted in five participating memory clinics over 18 months. To reach the goal of 544 dyads in total (108 per study center), each clinic must recruit six dyads per month. To mitigate the risk of under-recruitment, several strategies may be employed, including allowing over-recruitment at individual sites to compensate for under-recruitment at others, engaging additional memory clinics proximate to the current study centers into recruitment activities, sending study invitations to potentially eligible participants via collaborating health insurance providers, maintaining a “waiting list” of interested dyads who contact the clinic up to 6 months before the recruiting phase, and informing and involving general practitioners in each region to support referrals. Participants who provide written informed consent to participate will subsequently be included in the study.

## Assignment of interventions: allocation

### Sequence generation {16a}

The randomization will be conducted by the University Medicine Greifswald, Institute for Community Medicine using RandList software (Version 2, Datinf, Germany). Eligible dyads will be randomly assigned in a 1:1 ratio to the intervention or control group using computer-generated block randomization at the level of the memory clinics to ensure the parallelism of sampling, even in the case of under-recruitment. The clinics will receive the randomization lists in blocks of six.

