### Concealment mechanism {16b}

The allocation sequence will be performed by the evaluation team using RandList software. The randomization list will be accessible only to designated personnel within the project’s evaluation (internal) team of the Institute of Community Medicine (University Medicine Greifswald) and will be revealed after the baseline assessment is completed. All other study staff and investigators will have no access to the randomization list.

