## Assignment of interventions: blinding

### Who will be blinded {17a}

Study nurses capturing the outcomes will be blinded. However, due to the nature of the intervention, blinding is not feasible during the intervention period for Family Care Specialists and other staff of the memory clinic. Randomization will occur only after recruitment and baseline assessment are finalized. By maintaining concealment until this point, we mitigate potential selection bias and ensure that group assignment does not influence the initial evaluation of the dyads. Both caregiving experts and participating dyads will become aware of their group assignment once the intervention begins. As a result, the study is conducted with partial blinding, limited to the baseline assessment.

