### Limitations

A notable limitation of this study is the lack of participant and caregiver blinding, which is often unavoidable in complex psychosocial real-life interventions. This open-label design introduces a risk of performance and detection bias, as caregivers in the intervention group were aware of the additional support provided by the app and Family Care Specialists. Such awareness may result in a positive reporting bias (Hawthorne effect) [45], where participants might overestimate their perceived resilience (PTS) or underestimate their burden (ZBI) due to social desirability or high expectations. We estimate the potential magnitude of this bias to be moderate.

To mitigate this risk and ensure the robustness of our findings, we employed a triangulation strategy. By integrating objective secondary outcomes—specifically physiological hair cortisol levels as a marker of chronic stress and health insurance claims data to track the progression of care levels—we provide an empirical counterweight to the self-reported measures. The alignment of these objective parameters with subjective assessments allows for a more reliable interpretation of the intervention’s true clinical impact, reducing the likelihood that the observed effects are merely a result of reporting artifacts. 

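### The protocol both sends the randomisation lists to the clinics and denies clinic staff access to them, so allocation concealment is not assured

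*Protocol article*

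**What the plan says.** Sequence generation {16a} describes dyads "randomly assigned in a 1:1 ratio to the intervention or control group using computer-generated block randomization at the level of the memory clinics". It then adds: "The clinics will receive the randomization lists in blocks of six". Six is the only size named.

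Concealment mechanism {16b} says something different: "The randomization list will be accessible only to designated personnel within the" evaluation team, it "will be revealed after the baseline assessment is completed", and "All other study staff and investigators will have no access to the randomization list". Implementation {16c} only repeats which institute runs the sequence.

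Who will be blinded {17a} builds on this: "By maintaining concealment until this point, we mitigate potential selection bias". The same section says that "blinding is not feasible during the intervention period for Family Care Specialists and other staff of the memory clinic". The section on the coordinating centre and steering committee {5d} makes the five memory clinics responsible for recruitment, for carrying out the intervention and for data collection.

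**The concern.** One section puts the lists in the clinics' hands; the next says nobody outside the evaluation team can see them. The clinics recruit, and they learn the arm of each dyad once its intervention begins. If they also know, or can work out, the arm of the next dyad, they can influence who is enrolled and when. The eligibility criteria are broad, and the recruitment section allows a waiting list of interested dyads, so there may be some freedom over the order of entry.

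The primary outcome is a caregiver's own estimate of how long care can continue. Steering more or less strained caregivers towards one arm would therefore bear directly on it. The planned adjustment for notable baseline differences reaches only factors that were measured, so it cannot be relied on to remove selection of this kind. The trial is also open-label ("This open-label design introduces a risk of performance and detection bias", Limitations), so sound concealment is one of the main protections it has left.

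**Working it through.** There is no stated figure to reproduce. The check is a comparison of text, followed by a calculation of what each reading would imply.

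**Text, side by side**

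| Question | Sequence generation {16a} | Concealment mechanism {16b} |
|---|---|---|
| Who has the list? | The clinics | Designated evaluation-team personnel only |
| In what form? | Lists, in blocks of six | Not stated whether one allocation or the list is revealed |
| When? | Not stated | After the baseline assessment |

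No section mentions release of one allocation at a time, sealed envelopes, varying block sizes, or a recipient at the clinic who is separate from recruitment. Any of these might have reconciled the two.

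**Inputs:** 1:1 allocation, blocked within clinic, six named as the size (Sequence generation); 544 dyads, 108 per clinic (Recruitment). That is 108 / 6 = 18 blocks per clinic.

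**Reading A: the clinic holds the list for a block.** If it arrives before the first dyad, all six allocations are readable. If it is opened only after the first dyad's baseline, the next five are, so at least 5/6 = 83% are not concealed.

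**Reading B: the clinic never sees the list, but knows a constant block size of six and the block boundaries, sees all past allocations, and allocations are released one by one.** A 1:1 block of six has C(6,3) = 20 equally likely sequences.

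- The 4th is certain if the first three are alike: 2/20 = 0.10.
- The 5th is certain if the last two are alike: 2 × C(4,1)/20 = 8/20 = 0.40.
- The 6th is always certain: 1.
- Sum: 0.10 + 0.40 + 1 = 1.5 per block, and 1.5/6 = 25%.
- Per clinic: 18 × 1.5 = 27 of 108. Overall: 544 × 0.25 = 136.

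Guessing the arm with more places left, the chance of being right at each position is:

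| Position | Calculation | Probability |
|---|---|---|
| 1 | 1/2 | 0.5 |
| 2 | 3/5 | 0.6 |
| 3 | 0.4 × 3/4 + 0.6 × 1/2 | 0.6 |
| 4 | 0.1 × 1 + 0.9 × 2/3 | 0.7 |
| 5 | 0.4 × 1 + 0.6 × 1/2 | 0.7 |
| 6 | 1 | 1.0 |
| Sum | | 4.1 |

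So 4.1/6 = 68.3% of guesses are right, against 50% if allocation were unpredictable.

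**Reading C: a clinic receives a block's six results only after all six dyads have finished baseline.** Nothing is predictable, because every dyad in the block is already enrolled: 0 of 6.

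The share of allocations certain in advance thus runs from 0%, through 25%, to 83% or more, depending on a procedure that the text does not settle.

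**The case against.** The strongest reply is that the wording of {16a} is loose and practice may be sound. The concealment section places disclosure after baseline, and the blinding section says randomisation follows recruitment and baseline. With six dyads expected per clinic per month, a clinic could receive six results once six dyads have completed baseline (Reading C), or each allocation could be released singly. Six may be the batch in which lists are sent rather than the block length, and nothing says the size is constant or that sites know it. All of this stands. It does not remove the contradiction: what {16b} says will be revealed is the list, {16a} sends lists to clinics, and no sentence selects a benign reading. Finishing one dyad's baseline before disclosure protects that dyad only; it does not conceal later entries on a list already delivered.

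Two stronger readings are tempting. A reader might infer that clinics do see upcoming allocations and that concealment has failed. The documents show conflicting statements, not what the clinics were sent.

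A reader might also infer that staff could shade baseline scores according to the coming arm. That is weakly supported. Baseline interviews are done by study nurses described as unaware of assignment, the care is delivered by separate Family Care Specialists, the primary outcome and the caregiver burden score are self-assessed, and baseline precedes randomisation. What remains plausible is influence on whom to enrol and when.

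**Conclusion.** The two sections contradict each other, and the concealment claimed in {16b} and relied on in {17a} is therefore not assured. This is a conflict between two positive statements, not a detail that a journal article could leave to the full protocol. Taken literally, {16a} would expose at least five of every six allocations to unblinded recruiting clinics.

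The figures of 25%, about 136 of 544, and 68% hold only under Reading B: one constant block size of six, known to the sites, with block boundaries and past allocations tracked and single sequential release. They measure predictability. They are not an estimate of bias in the treatment effect or an expected loss, and under Reading C they fall to zero and to chance.

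The point is pressing because Trial status reports that recruitment started in January 2026 and is expected to run to July 2027. Any allocation already exposed cannot be concealed again.

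**What to change.** Reconcile Sequence generation {16a}, Concealment mechanism {16b} and Who will be blinded {17a}. Replace the sentence on clinics receiving lists with, for example: The evaluation institute holds the randomisation lists and releases each allocation singly, after that dyad's consent and baseline data are complete and locked. Withdraw any unreleased allocations that clinics already hold.

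As a cheap addition for dyads not yet randomised, use randomly varying block sizes within each clinic (for example 4, 6 and 8) and do not disclose them to sites. This is an enhancement and does not by itself resolve the contradiction. Simply choosing a larger known size would help little: the same enumeration for a constant known block of eight still gives 1.6/8 = 20% certain and 66.6% correct guesses.

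The cost is modest. The same institute and software can produce new lists, and dyads already randomised keep their allocation. Incomplete blocks at the switch and at the end of recruitment may leave a small imbalance in each of the five clinics. Under the protocol's own amendment rule, the change must go to all involved ethics committees and into the registration. If the current procedure already releases allocations singly from the centre, only the wording needs correcting.
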